## Abstract

**Introduction:**

Many women in low and middle-income countries enter pregnancy with low nutritional reserves with increased risk of fetal growth restriction and poor birth outcomes, including small-for-gestational-age (SGA) and preterm birth. Balanced energy–protein (BEP) supplements have shown reductions in risk of stillbirth and SGA, yet variations in intervention format and composition and limited evidence on the impact of BEP during lactation on growth outcomes warrant further study. This paper describes the protocol of the Maternal Infant Nutrition Trial (MINT) Study, which aims to evaluate the impact of a fortified BEP supplement during pregnancy and lactation on birth outcomes and infant growth in rural Nepal.

**Methods and analysis:**

MINT is a 2×2 factorial, household randomised, unblinded, efficacy trial conducted in a subarea of Sarlahi District, Nepal. The study area covers six rural municipalities with about 27 000 households and a population of approximately 100 000. Married women (15–30 years) who become pregnant are eligible for participation in the trial and are randomly assigned at enrolment to supplementation with fortified BEP or not and at birth to fortified BEP supplementation or not until 6 months post partum. The primary pregnancy outcome is incidence of SGA, using the INTERGROWTH-21st standard, among live born infants with birth weight measured within 72 hours of delivery. The primary infant growth outcome is mean length-for-age z-score at 6 months using the WHO international growth reference.

**Ethics and dissemination:**

The study was approved by the Institutional Review Board (IRB) at Johns Hopkins Bloomberg School of Public Health, Baltimore, USA (IRB00009714), the Committee on Human Research IRB at The George Washington University, Washington, DC, USA (081739), and the Ethical Review Board of the Nepal Health Research Council, Kathmandu, Nepal (174/2018).

**Trial registration number:**

NCT03668977.

WHAT IS ALREADY KNOWN ON THIS TOPICUndernourished women are at increased risk of fetal growth restriction and adverse birth outcomes, including preterm birth and small-for-gestational age.The WHO recommendations on antenatal care include balanced energy–protein (BEP) supplementation in undernourished populations to reduce the risk of stillbirth and small-for-gestational-age birth.WHAT THIS STUDY ADDSThe Maternal Infant Nutrition Trial (MINT) will demonstrate whether fortified BEP reduces risk of adverse pregnancy outcomes beyond multiple micronutrient supplementation.This study will also generate evidence on whether maternal intervention prevents early life infant growth faltering and improves maternal outcomes, such as anaemia and inadequate gestational weight gain.HOW THIS STUDY MIGHT AFFECT RESEARCH, PRACTICE OR POLICYMINT will help refine and implement the WHO context-specific recommendation on BEP supplementation in pregnancy.The trial will also provide evidence for potential intervention in pregnancy and post partum on infant growth outcomes.

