### Intervention

At enrolment, households are randomly allocated to either supplementation or not for the duration of pregnancy. Women in the supplementation group receive at home a supply of fortified BEP supplement for daily consumption beginning at 14 gestational weeks until the pregnancy outcome. Both groups also receive (1) recommendation to enrol in ANC at a local health clinic and deliver at a certified birthing facility; (2) nutrition, hygiene, and breastfeeding and infant care counselling; and (3) a clean birthing kit. In pregnancy, women in both groups are provided iron–folic acid tablets and albendazole, if not provided via ANC at their health facility. At the birth visit, households where a woman reports at least one live birth are randomly allocated to either supplementation or not for the postpartum period until the infant is 6 months old. Counselling for exclusive breastfeeding is provided in the postpartum period but iron–folic acid tablets are not provided as per the policy in Nepal.

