#### Composition of fortified BEP supplement

The fortified BEP supplement is a ready-to-eat snack in the form of lipid-based peanut paste packaged in individual sachets (72 g). The supplement was designed to meet the expert consensus specifications of a nutritious food supplement for pregnant and lactating women.^16^ Each sachet is a daily portion that provides calories (~400 kcal), protein (~14 g) and multiple micronutrients at the estimated average requirement for pregnancy. The product is made by Nutriset (France), as a specially manufactured version of their product known as ‘Plumpy’Mum’. We previously conducted two formative research studies to evaluate the acceptability of and adherence to various flavours of the BEP product in this community.^23 24^ Due to unavailability of raw materials, Nutriset produced three variations of Plumpy’Mum for use in our study, each with different combinations of ingredients selected to produce a product with a similar nutritional composition. The changes to the original ingredients were to remove the soy isolate (first change) and soy flour (second change), which resulted in minor changes in energy, protein and micronutrient concentrations, deemed inconsequential from a nutrition perspective. The specific ingredients and nutritional composition of each variation are provided in the online supplemental table 2.

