## Discussion

Nepal has made progress in reducing maternal, newborn and child mortality, but a significant burden of undernutrition remains among mothers and infants.^21 22^ Novel and effective interventions and practical implementation strategies are needed to prevent adverse pregnancy outcomes and infant growth faltering,^36 37^ and currently, the WHO^13^,^13^ recommends use of BEP supplements in undernourished settings, but standard formulations of such interventions and data on implementation in programmes are lacking. The MINT Study will provide evidence to help refine and implement the WHO context-specific recommendation on BEP supplementation in pregnancy, especially using the fortified, enhanced ready-to-use formulation recommended by the expert consensus on BEP supplements.^16^ As multiple micronutrient supplementation (MMS) reduces risk of adverse pregnancy outcomes, including LBW and SGA, our trial will contribute evidence as to whether the fortified BEP intervention, which includes the same 15 micronutrients, provides additional benefit beyond MMS alone.^38^ This trial will generate evidence on the potential of a maternal intervention to prevent early life growth faltering and improve maternal outcomes, such as anaemia and inadequate gestational weight gain, areas where a research gap exists. The results from the trial will inform health policy and programmes in Nepal, where there currently are no guidelines for community-level management of growth faltering in infants less than 6 months of age beyond exclusive breastfeeding. The primary strength of the trial is the 2×2 factorial randomised controlled trial design, which will enable understanding of the interconnections between maternal nutritional status in pregnancy and lactation and relationships to fetal and infant growth faltering. The trial includes frequent follow-up visits, over the continuum from early pregnancy to 6 months after delivery, which will generate data on many prenatal and postpartum factors that influence maternal and infant outcomes. The trial will describe maternal dietary intake, assess whether provision of BEP supplements leads to dietary substitution and measure adherence, yielding practical insights for implementation. Lastly, the trial structure allows for nesting various substudies, including those that assess the impact of BEP on the maternal and infant microbiome, infant neurodevelopment and maternal metabolites.

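### The key-message box promises an effect of fortified BEP beyond multiple micronutrients, but no arm is assigned multiple micronutrients, so the trial cannot identify that effect

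*Protocol article*

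**What the plan says.** The What this study adds box, printed after the trial registration number, says that MINT "will demonstrate whether fortified BEP reduces risk of adverse pregnancy outcomes beyond multiple micronutrient supplementation". The Discussion returns to the idea. It notes that multiple micronutrient supplementation (MMS) lowers the risk of adverse outcomes, naming low birth weight and SGA. It then says the trial will contribute evidence on whether the "fortified BEP intervention, which includes the same 15 micronutrients", "provides additional benefit beyond MMS alone".

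The Intervention section describes what the groups receive. In pregnancy, "women in both groups are provided iron–folic acid tablets and albendazole, if not provided via ANC at their health facility". Both groups also get the recommendation to attend antenatal care and deliver in a facility, a clean birthing kit, and "nutrition, hygiene, and breastfeeding and infant care counselling". The supplemented group additionally gets the sachet, which according to the composition section "provides calories (~400 kcal), protein (~14 g) and multiple micronutrients at the estimated average requirement for pregnancy".

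The Introduction words the first primary hypothesis as fortified BEP against no supplementation in pregnancy. The analysis section for primary aim 1 compares SGA between women allocated to the supplement and women not allocated to it, with the control group as referent.

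**The concern.** An effect beyond MMS is a difference between women who receive fortified BEP and women who receive MMS without the energy and protein. Estimating it needs a group assigned MMS, or some other arrangement in which the micronutrients are held constant while energy and protein vary. The article describes neither, yet its summary box tells readers that this trial will settle the question.

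The point is material because the Discussion itself says MMS reduces SGA, and SGA is the primary pregnancy outcome. On the article's own premise, some of any SGA benefit may come from the micronutrients in the sachet. Whether fortified BEP adds to iron–folic acid and whether it adds to MMS are different policy questions, and the article says its results will inform WHO and national policy. A valid answer to the first could be misread as an answer to the second.

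**Working it through.** This is a question of which contrast is randomised, so the main check is to set the arms side by side. There is no stated figure to reproduce.

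**Step 1. Contents of the pregnancy arms** (Intervention; Composition of fortified BEP supplement; Discussion)

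| Component | BEP group | Control group |
|---|---|---|
| Energy (~400 kcal) and protein (~14 g) | yes | no |
| Micronutrients in the sachet | yes | no |
| Iron–folic acid and albendazole, supplied by the study if not by antenatal care | yes | yes |
| Counselling, care recommendation, birthing kit | yes | yes |

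The rows common to both groups cancel. What remains is energy plus protein plus the sachet's micronutrients, always together.

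**Step 2. The other factor.** The postpartum factor is also fortified BEP or not. None of the four cells is assigned MMS or unfortified BEP. No cell comparison and no marginal comparison therefore holds micronutrients constant while energy and protein vary. Sharing the same 15 micronutrients with MMS does not help: they would cancel only if the controls received them too.

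**Step 3. What the estimate can and cannot tell.** Suppose, as an assumption, that effects multiply on the risk scale:

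RR(total) = RR(micronutrients) × RR(beyond micronutrients)

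The trial estimates only RR(total). Put in RR(total) = 1 − 0.175 = 0.825, from the 17.5% reduction in the Sample size section. The article gives no value for RR(micronutrients), so a range is assumed:

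| Assumed RR, micronutrients alone | RR beyond micronutrients | Share of the total log effect due to micronutrients |
|---|---|---|
| 1.00 | 0.825/1.00 = 0.825 | 0% |
| 0.95 | 0.825/0.95 = 0.868 | ln 0.95/ln 0.825 = 27% |
| 0.90 | 0.825/0.90 = 0.917 | ln 0.90/ln 0.825 = 55% |
| 0.85 | 0.825/0.85 = 0.971 | ln 0.85/ln 0.825 = 84% |

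Every row gives the same comparison of SGA between the randomised groups. A larger sample would narrow the interval around 0.825 but would not choose between the rows.

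**The case against.** The strongest reply is that every operative part of the article states the contrast correctly. The aim, the hypotheses, the study design and the analysis all refer to fortified BEP against no supplementation. No outcome, sample size or model depends on the MMS statement, and the abstract does not make it. All of this stands, and it limits the point to inferential wording in two places.

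A second reply is that the Discussion promises only to contribute evidence, and the dissemination plan foresees meta-analyses with similar trials. Pooling might indeed inform the question if other trials had an MMS comparator. That reading makes the Discussion sentence defensible once it is qualified, although the article does not say this is what it means. It does not rescue the box, which says this trial will demonstrate the effect.

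Three stronger readings are tempting but unsupported:

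- A reader might infer that the primary SGA comparison is invalid. It is not. It is a sound randomised comparison of the package plus iron–folic acid with iron–folic acid.
- A reader might infer that a positive result will be reported as benefit beyond MMS. The analysis section commits only to a relative risk against the control group. The documents support a risk of misreading, not a forecast.
- A reader might infer that the micronutrients could explain the whole effect. In the illustration that would need a micronutrient relative risk of 0.825, which lies outside the assumed range. The documents give no value that supports or excludes it.

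**Conclusion.** The point holds as a contradiction between a stated inference and the design. The effect of fortified BEP beyond MMS is not identifiable from any comparison within this trial, and no analysis plan could recover it, because no group is assigned the needed comparator. The box is wrong as written. The Discussion sentence is weaker and needs deletion or qualification.

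Severity is moderate. The primary test, its estimate and its power are untouched; what changes is the conclusion the trial may claim. The arm comparison rests only on the article's description of care. The numerical range rests on three assumptions: the micronutrient relative risks, multiplicative effects, and the sachet's micronutrients being equivalent to MMS. It shows how far apart the possible answers could lie and does not estimate any of them.

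**What to change.** 1. In the What this study adds box, remove the claim of an effect beyond multiple micronutrient supplementation.
2. In the Discussion, delete the corresponding statement, or qualify it as a question that only pooling with trials that have an MMS comparator could inform.
3. State the pregnancy contrast once, in plain terms: fortified BEP (energy, protein and micronutrients as one package) plus iron–folic acid, versus iron–folic acid, with other care common to both groups.
4. Add a sentence saying that the trial cannot separate the energy–protein effect from the micronutrient effect.

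Comparator, care, sample size and analysis stay as they are. The cost is a few sentences and a narrower stated claim.

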## Introduction

Many women in low and middle-income countries (LMICs) enter pregnancy with low nutritional reserves, unable to meet the increased requirements for protein, energy, and micronutrients during pregnancy and lactation. Undernourished women are at increased risk of fetal growth restriction and adverse birth outcomes, including preterm birth (<37 gestational weeks) and small-for-gestational-age (SGA) (birth weight <10th percentile of a reference standard by gestational age and sex), two underlying biological causes of low birth weight (LBW) (<2.5 kg).^1^ SGA infants are more likely to experience higher mortality, linear growth faltering and poor health outcomes, poor cognitive performance, and diminished educational and employment attainment.^2–4^ In 2020, 23.4 million infants (17.4% of all births) were born SGA, with the highest prevalence in South Asia (40.9%).^5 6^ Estimates from 2012 indicate that 22% neonatal deaths in LMICs, and 26% in South Asia, were attributable to SGA.^7 8^

Infant size status at birth and growth in the first 6 months of life, especially among preterm and SGA infants, are critical determinants of childhood stunting and wasting associated with higher risk of mortality, morbidity and poor developmental outcomes.^9^ Many maternal risk factors associated with pregnancy outcomes and consequent preterm or SGA are likely contributors to linear growth failure.^10^ Postnatal factors, such as breastfeeding and feeding behaviours, infections and environmental factors, are also important drivers of infant growth.^11 12^

Nutritional interventions targeted to women during pregnancy and lactation provide an opportunity to break the intergenerational cycle of growth failure. The WHO recommendations on antenatal care (ANC) include balanced energy–protein (BEP) supplementation in undernourished populations to reduce the risk of stillbirth and SGA birth.^13^ This is based on a systematic review of BEP supplementation during pregnancy that has shown decreased risk of stillbirth (relative risk (RR): 0.60, 95% CI: 0.39 to 0.94) and SGA (RR: 0.79, 95% CI: 0.69 to 0.90).^14^ BEP also increased mean infant birth weight by 41 g overall and 100 g among undernourished women.^14 15^

Despite this context-specific recommendation, the variations in formats, ingredients and nutrient composition have hindered programmatic progress. Further, there is no recommendation for supplementation of women who are breastfeeding, despite high rates of growth faltering in early life in LMICs, where maternal undernutrition is high and exclusive breastfeeding is recommended in the first 6 months of life. Recently, an expert consensus developed specifications for a fortified BEP ‘ready-to-use’ food supplement for pregnant and lactating women in LMICs.^16^ Such a product requires testing in undernourished settings for efficacy in improving birth outcomes and infant growth.

In this paper, we describe the study protocol for the Maternal Infant Nutrition Trial (MINT) at the Nepal Nutrition Intervention Project Sarlahi (NNIPS) research site in Sarlahi District, Nepal. The aim of the MINT Study is to evaluate the efficacy of daily fortified BEP supplementation during pregnancy and lactation on SGA and mean length-for-age z-score (LAZ) in the first 6 months of life. In this rural population, there is a significant burden of undernutrition among mothers and infants and high prevalence of adverse pregnancy outcomes.^17–19^ However, breastfeeding through 6 months of life is high, presenting postpartum supplementation as a plausible mechanism by which to improve infant growth. Our primary hypotheses are that (1) fortified BEP supplementation versus no supplementation during pregnancy will reduce incidence of SGA, and (2) fortified BEP supplementation versus no supplementation during lactation alone or both during pregnancy and lactation will improve infant linear growth in the first 6 months after delivery. Several secondary outcomes will also be examined.

## Methods and analysis

### Study design

MINT is a 2×2 factorial, household randomised, unblinded, efficacy trial of fortified BEP supplementation versus no supplementation among women during pregnancy and lactation on SGA and infant growth to 6 months after delivery in rural Nepal (figure 1). This community-based trial began in November 2021, and will enrol approximately 1800 mother–fetus/infant pairs over the course of about 20 months.

**Figure 1 F1:**
[figure not shown]
MINT Study design. MINT, Maternal Infant Nutrition Trial.

We nested several substudies within the trial to explore the impact of the intervention on maternal dietary intake during pregnancy and post partum, infant neurodevelopment at 6 months after delivery, metabolites in blood during pregnancy, and the gut microbiota among mothers in pregnancy and infants in the postnatal period.

This protocol follows the Standard Protocol Items: Recommendations for Interventional Trials guidelines (online supplemental table 1).^20^

10.1136/bmjpo-2023-002229.supp1Supplementary data

### Study setting

The MINT Study is conducted in Sarlahi District, Madhesh Province, in the Terai region (low-lying plains) of Nepal by the NNIPS research team. The NNIPS field research site, established in 1989 and covering approximately one-third of the district, currently operates as a joint undertaking between the Department of International Health, Johns Hopkins Bloomberg School of Public Health, and the non-profit organisation, Nepal Netra Jyoti Sangh, under a memorandum of agreement with the Social Welfare Council, Government of Nepal. Nepal’s Terai region has high rates of maternal undernutrition, neonatal mortality, adverse pregnancy outcomes and inadequate infant growth, and is representative of rural, low-income settings in much of South Asia.^21^ Over half (56.9%) of households in Nepal’s Madhesh Province faced food insecurity with 10% being severely food insecure, according to the Nepal Demographic and Health Survey 2016.^21^ Of children under 5 years old, 29.3% were stunted and 10.1% were wasted in Madhesh Province in 2022.^22^ Data from our most recent trial in the NNIPS study area, which had over 31 000 live births (2010–2017), reported neonatal mortality and stillbirth rates of approximately 32 per 1000 live births and 29 per 1000 births, respectively (unpublished). In that trial, the proportion of adverse pregnancy outcomes were: preterm birth 14.9%, SGA 48.5% and LBW 30.1% (unpublished). Nearly one-third of women in their first trimester of pregnancy were underweight (29.5%) (body mass index (BMI) <18.5 kg/m^2^) and the same proportion (29.5%) had a height less than 145 cm (unpublished). Over one-third of infants (35%) are breastfed within an hour of birth and 95% within 24 hours in our trial population (unpublished).

### Study population and recruitment

The study area includes 34 wards selected from six rural municipalities (Haripur, Ishwarpur, Kabilasi, Malangawa, Chakraghatta and Chandranagar) with a population of approximately 100 000 people. MINT enumerated and recruited participants through a household census and pregnancy surveillance system. Due to disruptions caused by the COVID-19 pandemic, the trial census and enrolment were divided into two periods.

In July 2019, we conducted a census to enumerate the households in the study area with potentially eligible women. The census activity identified about 27 000 total households, including roughly 13 000 households with at least one woman meeting the eligibility criteria for pregnancy surveillance. The first enrolment period spanned November 2021–June 2022, enrolling 938 women.

Between the original census and the start of pregnancy enrolment (which was delayed due to the COVID-19 pandemic), many newly married women accumulated in the study area. In December 2022 and January 2023, we conducted a new household census update activity to add these newly married women, who would be eligible for enrolment in the trial, to our census and pregnancy surveillance roster. The census update activity added about 1400 newly married women to the census roster for a total of around 14 400 women eligible for pregnancy surveillance and subsequent enrolment if they become pregnant. The second enrolment period began in January 2023 and will run until the sample size of 1800 women is met.

Pregnancy surveillance is conducted by local, female data collectors hired on the project to make household visits every 5 weeks to ask potential participants if they had a period since the last visit and offer a urine-based pregnancy test if not. All married women (15–30 years) resident in the study area at the time of the census who are identified as pregnant by our pregnancy surveillance system (<24 weeks’ gestation) and consent to participate are eligible for participation in the trial. Women who self-report an allergy to nuts, milk or soy at enrolment are excluded.

We have enrolled 1944 women as of August 2023.

